|             |             | 
4. Section 9.1: Removed seizures from the MDRI and list of choices for 2 most bothersome problems. Also changed measurement of seizure outcome to continuous real-time recording by caregivers.
 
Rationale: We have found seizures are uncommon in our cohort and if present, are well controlled on anti-epileptics and/or so sporadic that the 1-week logs are not adequately capturing this outcome. Given the rarity of these, we believe capturing each event during the entire study will provide a better evaluation of this outcome.
                                                                                                                                                                                                                                                                                                                                                                                                                                                                                                                                                                                                                                                                                                                                                                                                                                                                                                                                                                                  |

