- Autism **Parenting Stress** Index (APSI): MCID = 0.25 SD for Stress Total 
  - Ability to communicate
  - Tantrums/meltdowns
  - Self-injurious behavior
  - Difficulty making transitions from one activity to another
  - Toilet training
  - Not feeling close to your child
  - Concern for your child not being accepted by others
  - Concern for the future for your child living independently
- PROMIS **Fatigue** - Parent Proxy Custom Short Form: MCID = 3-point change
- **Seizures** – Parents will record each seizure in a seizure journal provided by the study. Information recorded will include the duration (average length of seizure), and need for medical intervention (e.g. rescue medication, medical evaluation).

- **Movement** disorder (e.g. dystonia, chorea, etc.) – Parent reported duration and severity. Change in one of two characteristics for +/-1 score, +/-2 score for change in two of the characteristics.
- Non-communicating Children's **Pain** Checklist-Revised (NCCPC-R): MCID = 0.25 SD

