| Sanfilippo Behavior Rating Scale                       |           | X                               | X                 |                                                              | X                                | X                                      |
| Non-communicating Children's Pain Checklist-Revised    |           | X                               | X                 |                                                              | X                                | X                                      |
| Parent reported outcomes (PROMIS) d         |           | X                               | X                 |                                                              | X                                | X                                      |
| Seizure - parent assessment x 1 week                   |           | X h                  | X                 |                                                              | X                                | X                                      |
| Movement - parent assessment x 1 week                  |           | X h                  | X                 |                                                              | X                                | X                                      |
| Individual Clinical Response                           |           | X                               | X                 |                                                              | X                                | X                                      |
| Gait assessment                                        |           | X                               | X                 |                                                              | X                                |                                        |
| Vineland-III                                           |           | X                               |                   |                                                              | X                                |                                        |
| Stair climb                                            |           | X                               | X                 |                                                              | X                                |                                        |

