f After written informed consent but before study treatment initiation, only SAEs associated with protocol-imposed interventions will be recorded. After study drug initiation, all AEs, SAEs, and pregnancy will be recorded until week 44 or the Early Termination visit. If a subject is discontinued from the study prematurely, AEs and SAEs will be recorded at the Early Termination visit.

g During these contacts, study staff will ask about dose administration and seek information on AEs and SAEs by specific questioning. Information on all AEs and SAEs should be recorded in the subject's medical record and on the AE eCRF.

h Diaries will be completed at week -6 to avoid the potential impact of travel on these outcomes.

i Plasma and serum samples collected and stored for PK and anti-drug antibody studies.

j Buffy coat will only be collected on Week -8, Day 1, and Week +36.

k Week +24 safety labs only if dose was increased at week +16.

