### **10.12 Seizures**

Seizure frequency, duration, and severity will be reported by the caregiver in real time in a study diary or by texting the research group (based on caregiver preference).

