### **10.13 Disordered Movement**

The duration, severity, and type (e.g. dystonia, chorea) of movement abnormality will be reported by the caregiver in real time for 1 week at a time in a survey. Duration will be quantified as:

- ☐ Occasional (<25% of the time)
- ☐ Intermittent (25-50% of the time)
- ☐ Frequent (50-75% of the time)
- ☐ Constant (>75% of the time)

Severity will be quantified as:

- ☐ The movement has interfered more with my child's daily activities
- ☐ The movement has interfered less with my child's daily activities
- ☐ No change in the severity of the abnormal movement

Optional: The parents can take a short, representative video of the movement disorder on the days they are recording it as above.

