## 12.2 Analysis

### **Primary objective**

Outcome variables include AEs/tolerability, 2 most bothersome symptoms, and multi-domain responders index (MDRI) as described in section 9.1. Binary AEs such as hospitalization ( $\geq 1$ ) will be summarized using frequencies/rates by the two period (pre-observation, treatment). The multiple event such as the total number of seizures will be summarized using median with the inter-quartile range (IRQ). For testing changes between the two periods, the McNemar's test (binary event) or Wilcoxon Signed Rank test (multiple events and MDRI) will be used. For continuous outcomes such as laboratory results, a paired t-test and a repeated measures ANOVA will be used. Residual analyses will be conducted to check the model assumption. If it violates assumption, Friedman test (nonparametric) will be used instead.

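### The Schedule of Events still has seizures logged for one week at a time, while Sections 9.1 and 10.12 have every seizure recorded, so the seizure count tested in Section 12.2 has two different bases

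*Protocol*

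**What the plan says.** Four current parts of the protocol bear on how seizures are counted.

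- **Section 10.2, Schedule of Events.** The row reads "Seizure - parent assessment x 1 week" and is marked at Week -8, Day +1, Weeks +8 and +16, Week +36 and Week +44. Footnote h is attached to the Week -8 entry: "Diaries will be completed at week -6 to avoid the potential impact of travel on these outcomes".
- **Section 9.1, primary endpoints.** "Parents will record each seizure in a seizure journal provided by the study". No weekly limit is given.
- **Section 10.12.** "Seizure frequency, duration, and severity will be reported by the caregiver in real time in a study diary or by texting the research group". Again there is no weekly limit. The next section, on disordered movement, does set one: those data "will be reported by the caregiver in real time for 1 week at a time in a survey".
- **Section 12.2, primary objective.** "The multiple event such as the total number of seizures will be summarized using median", with the inter-quartile range. Multiple events are then compared between the pre-observation and treatment periods by the Wilcoxon signed rank test.

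As background only, the Version 1.7 entry in Section 1.0 reads "Also changed measurement of seizure outcome to continuous real-time recording by caregivers". Its stated reason is that seizures were too sporadic for 1-week logs to capture.

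**The concern.** A site working from the table would collect six isolated weeks of seizure data per child. A site working from Sections 9.1 and 10.12 would collect all 52. Both are following the protocol. Section 12.2 uses a total and does not tie it to the days on which seizures were being recorded, so the same child can yield very different counts under the two rules.

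An analysis plan cannot repair this later. It can define a rate, but it cannot recover seizures that nobody was asked to write down. The adverse-event record does not fill the gap before treatment either: footnote f to the schedule limits pre-dose recording to serious events tied to protocol-imposed interventions. The log or journal is therefore the only prospective seizure count that the protocol specifies for the pre-treatment period, and that period is the comparator.

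**Working it through.** The protocol states no figure that depends on this point, so there is none to reproduce. The check is a count of observed weeks under each rule.

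**Inputs**
- Period lengths (Section 10.1): 8 weeks before treatment, 36 weeks on treatment, 8 weeks after; 52 in all.
- Logs under the schedule: six, at Week -8 (kept in week -6 under footnote h), Day +1, and Weeks +8, +16, +36 and +44.
- Placement of the later logs: Section 10.6 puts the sleep diary in the week before each visit. Nothing equivalent is stated for seizures, so applying it to them is an assumption. The entry that matters is Day +1, so it is taken both ways; the other later logs are taken as falling before their visits.

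**Weeks observed**

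| Rule | Pre-treatment (8) | Treatment weeks 0-8 (8) | Treatment weeks 0-36 (36) | Whole study (52) |
|---|---|---|---|---|
| Schedule, Day +1 log before the visit | 2 | 1 | 3 | 6 |
| Schedule, Day +1 log after first dose | 1 | 2 | 4 | 6 |
| Sections 9.1 and 10.12 | 8 | 8 | 36 | 52 |

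**Results if the schedule is followed throughout**
- Whole-study coverage: 6/52 = 11.5%.
- An 8-week period with 1 log week: 7/56 days = 12.5% observed, so 87.5% of seizures are missed at a constant rate.
- An 8-week period with 2 log weeks: 14/56 days = 25% observed, so 75% are missed.
- Ratio of expected raw totals, treatment weeks 0-8 to pre-treatment, at an unchanged rate: 1/2 or 2/1, depending on the Day +1 log. Against the full 36 weeks it is 3/2 or 4/1.

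**Chance of recording no seizures.** The protocol gives no seizure rate, so a range is assumed. With Poisson counts, P(none) = exp(-rate × weeks observed / 8).

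| Assumed seizures per 8 weeks | 1 log week | 2 log weeks | All 8 weeks |
|---|---|---|---|
| 0.5 | 94% | 88% | 61% |
| 1 | 88% | 78% | 37% |
| 2 | 78% | 61% | 14% |
| 4 | 61% | 37% | 2% |

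For sporadic seizures, the logs would mostly return zeros whatever the drug does.

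**A mixed case.** For a child with logs before treatment and a continuous journal over treatment weeks 0-8, the apparent ratio at an unchanged rate is 8/2 = 4 or 8/1 = 8.

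**The case against.** The strongest reply is that the intended rule can be recovered. Two body sections agree, Section 10.12 omits the weekly limit that Section 10.13 states, and the table row looks like a label that was not updated. That is probably right, and it shows which way to reconcile. It does not remove the conflict, because the Schedule of Events is what staff and families work from visit by visit.

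A second reply is that the impact is limited. Most of this stands. The Version History calls seizures uncommon in the cohort. They have no minimal clinically important difference in Section 9.1, are absent from its list of responder-index components under the secondary endpoints, and appear in Section 12.2 only as an example. After dosing starts, all adverse events are recorded, families are contacted every 4 weeks with specific questions, and seizures are named among the expected events in Section 13.2. New or worsening seizures on treatment therefore need not go unseen between log weeks. This route does not supply a count, however, and it does not cover the pre-treatment period.

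A third reply is that rates and denominators can be left to an analysis plan. That is fair for the details, but not for the choice of collection rule, which the protocol sets twice.

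A reader might go further and infer a spurious 4- to 8-fold rise in seizures on drug. The document does not support that as a general consequence. No current passage changes the method at Day +1: the table applies logs at every visit, and Sections 9.1 and 10.12 apply one rule throughout. Such a rise needs a child whose method changed between periods, for example around Version 1.7. The document does not say whether or how often this happened.

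**Conclusion.** The conflict is real and lies between passages in force; it does not depend on the amendment log. Followed as written, the table observes about 11.5% of the study, misses 75% to 87.5% of seizures in each 8-week period at a constant rate, and makes raw totals differ 2:1 between the two 8-week periods with no change in the child. The direction of that imbalance depends on the placement of the Day +1 log, which is an assumption here. Coverage is not one week in every 8-week period, as a quick reading of the row might suggest: both the week -6 and the Day +1 logs are scheduled, so one of the two periods has two.

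The point should be corrected, but it is of modest weight given how rare seizures are said to be and the other on-treatment capture. It does not invalidate the trial's main comparisons.

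**What to change.** - In the Schedule of Events, change the seizure row to continuous recording from Week -8 to Week +44 and detach footnote h from that row, so that it agrees with Sections 9.1 and 10.12. Footnote h can stay on the movement and sleep-diary rows.
- Record the dates on which each child's journal or log was active.
- In Section 12.2, compare seizures per observed day in each period instead of raw totals. For any child with only 1-week logs in a period, use the logged days as the denominator. No child needs to be left out of the paired test on this account.

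The cost is one table row, one pair of date fields and a rate in place of a total. The rate also allows for the unequal period lengths if the full 36 weeks are compared with the first 8: even with complete recording, raw totals would then differ by 36/8 = 4.5 at a constant rate.

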### 3.0 Objectives

The primary objectives of the study are to:

1. Evaluate the safety and tolerability of anakinra in children age  $\geq 4$  years with MPS III, defined by the incidence of treatment-emergent adverse events and abnormal laboratory values, and number of subjects withdrawn due to intolerability (e.g. unable to administer SC injection to subject, worsening behaviors).
2. Evaluate the effect of anakinra on a multi-domain responder index (MDRI) as a means to determine need for dose escalation. Due to the inherent heterogeneity of disease presentation, the MDRI will measure change tailored to patient-specific symptoms. MDRI change will inform dose-finding by reflecting lack of change in clinical outcome. The MDRI will be composed of the following:
  - Sanfilippo Behavior Rating Scale (SBRS)
  - Child Sleep Health Questionnaire (CSHQ)
  - Autism Parenting Stress Index (APSI)
  - PROMIS Fatigue - Parent Proxy Custom Short Form
  - Seizures – parent reported frequency, duration, and severity
  - Movement disorder (e.g. dystonia, chorea, etc.) – parent reported frequency, duration, and severity
  - Non-communicating Children's Pain Checklist-Revised (NCCPC-R)

The secondary objectives of the study are to evaluate the effect of anakinra on:

- Individual Clinical Response (ICR) – 5 most impactful clinical problems reported by the caregiver
- Gait
- Stair climb/descent
- Sleep Diary (1-week recall)
- Sanfilippo Syndrome Stool Habit Questionnaire

The exploratory objectives of the study are to evaluate the effect of anakinra on:

- ☐ Stool microbiome
- ☐ Vineland Adaptive Behavior Scales, Third Edition (VABS-III)

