### **6.0 Study-Wide Number of Subjects**

Twenty (20) subjects will be enrolled in this pilot study. Individuals who withdraw before Week +8 will be replaced.

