## 9.0 Study Endpoints

### 9.1 Primary and secondary endpoints.

#### Primary endpoints:

Phase 1: Incidence of treatment-emergent adverse events and laboratory values over 8 weeks of treatment to known frequency of anakinra-related AEs in other populations.

Phase 2: Need for dose escalation as determined by within individual change over 8-week treatment period compared to change over 8-week observational period in the 2 most bothersome symptoms for each enrolled patient, selected from measures for the MDRI. Choices are below in bold. These 2 symptoms will be monitored by one or more of the assessments below. If the Minimal Clinically Important Difference (MCID) that is defined below is not achieved after 8 weeks of treatment, or there has been a decrease of more than the MCID between 8 and 16 weeks after an increase greater than MCID at week 8, the dose will be escalated (see Section 27.7). If the MCID is not achieved after 8 weeks on maximum trial dose of 200mg (max dose 8 mg/kg/day), treatment with anakinra may be discontinued (see Section 27.7).

- Sanfilippo **Behavior** Rating Scale (SBRS): MCID = 0.25 SD for each scale
  - Symptoms described in table below:

|                         |                                                                                                                                        |                           |
|-------------------------|----------------------------------------------------------------------------------------------------------------------------------------|---------------------------|
| Body Movements          | Makes large complex movements of their body, such as spinning, twirling or repeatedly bouncing up and down.                            | Movement                  |
| Object Interaction      | Examines or manipulates some novel or unfamiliar objects repeatedly.                                                                   |                           |
| Activity/Routines       | Never plays with one object or engages in one activity for very long.                                                                  |                           |
| Emotional Function      | Expresses emotions inappropriate to the situation.                                                                                     | Social/emotional function |

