| Whole Blood                                            |           | X                               | X                 |                                                              | X                                | X                                      |
| Anakinra e                                  |           |                                 |                   |                                                              |                                  | X (week 8 and 16 only)                 |
| Adverse events f                            |           | X                               | X                 |                                                              | X                                | X                                      |
| Contact for study follow up g               |           | Required every 4 weeks ± 7 days |                   |                                                              |                                  |                                        |

a If sponsor discontinues the study at any time, or a subject is discontinued from the study after week +8 and before week +44, an early termination visit will be done. Early termination visit procedures will be the same as for the week +44 visit.

b All procedures/intervention/surgery due to underlying MPS III will be recorded after informed consent is obtained, until week 44 or the Early Termination visit. If a subject is discontinued from the study prematurely, all procedures/intervention/surgery due to underlying MPS III will be recorded at the Early Termination visit.

c All medications (prescription, over-the-counter and herbal) and nutritional supplements taken 30 days prior to Screening and throughout the study should be documented.

d PROMIS surveys are the Autism Parenting Stress Index (APSI) and a customized Parent Proxy Fatigue – Short Form.

e The same injection site should not be used 2 days in a row, and should be rotated between the four injection sites (upper thigh, upper back of arm, abdomen or buttocks). Dose will be escalated at week 8 and 16, or decreased at any time, per protocol described in Section 27.7 Dosing.

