### **13.0 Provisions to Monitor the Data to Ensure the Safety of Subjects**

The plan for ensuring subject safety will include the following elements:

1. Clinical procedures will only be performed by properly trained personnel who are qualified by training and licensure to perform the procedures.
2. Investigator and all study personnel have completed required training regarding Human Subject Protections. All personnel will comply with all related regulations and laws.
3. Patients will be rigorously screened against inclusion/exclusion criteria to ensure that their participation is safe.
4. Adverse events and SAEs will be assessed and followed throughout study. Subjects will have contact information to enable them to contact study personnel easily and quickly.
5. Study data and information will be kept confidential and managed in accordance with requirements of Health Insurance Portability and Accountability Act of 1996 (HIPAA). All data will be stored in locked offices and not released without subject permission.
6. Subject may discontinue participation at any time, for any reason. Any subject who fails to complete the research procedures within acceptable parameters, or is unable to safely tolerate participation in the study will be withdrawn.
7. Institutional Review Board approval and IND approval will be obtained.
8. Monitoring will be conducted by the research team, institutional review board (IRB) and independently (i.e. at a minimum of annually) by qualified staff of Harbor-UCLA Clinical and Translational Science Institute (CTSI) in accordance with the established Monitoring Plan.
9. The PI will allocate adequate time for such monitoring activities and will ensure that the monitor or other compliance or quality assurance reviewer is given access to all study-related documents and study related facilities (e.g. pharmacy, diagnostic laboratory, etc.) and has adequate space to conduct the monitoring visit.

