## **14.0 Withdrawal of Subjects**

Subjects will be encouraged to complete the study; however, they may voluntarily withdraw at any time. If a subject is withdrawn prior to study completion, attempts will be made to schedule and conduct an Early Termination visit for medical assessment. If a subject cannot be contacted after 5 telephone calls and 3 letters/emails, they will be considered lost to follow-up.

Subjects who discontinue study medication (e.g. due to non-compliance, AEs, etc.) will be asked to remain in the study for follow-up per the study schedule to preserve the ability to perform an intent to-treat (ITT) analysis. If a subject or their legal guardian (as applicable) withdraws consent to participate in the study, attempts will be made to obtain permission to record survival and adverse event (malignancy, hospitalization for infection) data at the Week +44 study point.

Study drug will be discontinued in any subject meeting the following criteria for drug-induced liver injury:

- ☐ ALT or AST > 8x upper limit of normal (ULN)
- ☐ ALT or AST > 5x ULN for more than 2 weeks
- ☐ ALT or AST >3x ULN and (total bilirubin >2x ULN or INR > 1.5)
- ☐ ALT or AST >3x ULN with the appearance of fatigue, nausea, vomiting, right upper quadrant pain or tenderness, fever, rash, and/or eosinophilia (>5%)

Management of suspected drug-induced liver injury will be consistent with the FDA Guidance for Industry Drug-Induced Liver Injury: Premarketing Clinical Evaluation. Specifically, an increase of ALT or AST of >3x ULN will be followed by repeat testing within 48-72 hours of ALT, AST, alkaline phosphatase, and total bilirubin level. There will be inquiry made about symptoms. If symptoms persist or repeat testing shows ALT or AST >3x ULN close observation to determine whether the abnormalities are improving or worsening will be initiated as follows:

- ☐ Repeating liver enzyme and serum bilirubin tests two or three times weekly. Frequency of retesting can decrease to once a week or less if abnormalities stabilize or the trial drug has been discontinued and the subject is asymptomatic.
- ☐ Obtaining a more detailed history of symptoms and prior or concurrent diseases.
- ☐ Obtaining a history of concomitant drug use (including nonprescription medications and herbal and dietary supplement preparations), alcohol use, recreational drug use, and special diets.

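### Exit visits before Week +8 are defined inconsistently, and the tolerability count in primary objective 1 depends on which withdrawal passage the site follows

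*Protocol*

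**What the plan says.** **Exit visit.** Protocol 10.2, Table 1 footnote a, provides the visit if "a subject is discontinued from the study after week +8 and before week +44, an early termination visit will be done", or at any time if the sponsor stops the study. It sets the content as the Week +44 procedures, and Table 1 and 10.4 include safety labs at Week +44. Section 14.0 has no Week +8 limit: "If a subject is withdrawn prior to study completion, attempts will be made to schedule and conduct an Early Termination visit". Section 10.20 says much the same for a subject who opts to discontinue. Both describe the purpose only as medical assessment. Footnote f has the AEs and SAEs of a prematurely discontinued subject recorded at the early termination visit.

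**Withdrawal and intolerance.** Section 13.0 item 6 says a subject who "is unable to safely tolerate participation in the study will be withdrawn". Section 14.0 says that subjects who stop study drug, with AEs among the examples, "will be asked to remain in the study for follow-up per the study schedule". Section 6.0 adds: "Individuals who withdraw before Week +8 will be replaced".

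**What depends on these passages.** The Phase 1 primary endpoint (9.1) is "Incidence of treatment-emergent adverse events and laboratory values over 8 weeks of treatment". Primary objective 1 (3.0) also counts the "number of subjects withdrawn due to intolerability", with inability to give the injection and worsening behaviour as examples.

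**Denominators.** Section 6.0: "Twenty (20) subjects will be enrolled in this pilot study". Section 12.1 puts everyone who receives any treatment in the safety population and uses that population for the primary analyses. Section 12.2 ties the descriptive statistics to a total cohort of N=20.

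**The concern.** Weeks 0 to 8 are the primary safety window, and the only passage that fixes the content of an exit visit leaves that window out. A site working from Table 1 has no scheduled exit labs for a child who stops coming at, say, Week +3 or Week +7, and footnote f sends the closing AE record to a visit that footnote a does not provide.

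The second problem is one of counting. The tolerability measure in objective 1 is expressed as withdrawals. One passage turns intolerance into withdrawal, and another asks the child who stops drug to stay. The same clinical course may then be counted or not, and the child replaced or not, according to the passage followed. With about 20 children, one case is 1/20 = 5 percentage points.

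**Working it through.** **1. Exit-visit passages side by side, for a dosed child leaving before Week +8**

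| Source | Visit before Week +8? | Content fixed? |
|---|---|---|
| 10.2 footnote a | Not provided | Week +44 procedures, including safety labs (only after Week +8) |
| 10.20 and 14.0 | To be attempted | Medical assessment only |
| 10.2 footnote f | Assumed to take place | Recording of AEs and SAEs |

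Read together, they give at best an attempted visit with no stated labs.

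**2. Age of the last scheduled lab at exit.** Section 10.4 places on-treatment labs at Weeks +2, +4 and +8.
- Exit at Week +3: last lab at Week +2, so 3 − 2 = 1 week old.
- Exit at Week +7: last lab at Week +4, so 7 − 4 = 3 weeks old.
- Upper limit: just under 8 − 4 = 4 weeks.

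**3. The tolerability count.** The protocol gives no expected number of early stops; take k = 1 to 4 as an assumption. If every such child stays in the study as 14.0 asks, none is withdrawn and none is replaced: 0/20. If every one is withdrawn under 13.0 item 6 and replaced under 6.0, the count is k/(20 + k).

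| k | All stay (14.0) | All withdrawn and replaced (13.0, 6.0) |
|---|---|---|
| 1 | 0/20 = 0% | 1/21 = 4.8% |
| 2 | 0/20 = 0% | 2/22 = 9.1% |
| 3 | 0/20 = 0% | 3/23 = 13.0% |
| 4 | 0/20 = 0% | 4/24 = 16.7% |

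These are the two extremes; a mixture falls between them. For k = 2 the exact (Clopper-Pearson) 95% intervals are 0 to 16.8% and 1.1 to 29.2%.

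**4. The denominator.** Section 12.3 states a margin of error of 13% to 18% at n = 20 for proportions of 5% to 15%. A continuity-corrected Wilson interval gives half-widths of 13.3% (1/20) and 17.5% (3/20), so that figure is reproduced within one point and is not in dispute. It assumes 20 treated children, however, and replacement makes the treated number 20 + k.

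Suppose m = 1 of the 20 retained children has an event and all k replaced children have it. Leaving out the replaced children gives m/20; the safety population of 12.1 gives (m + k)/(20 + k).

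| k | Replaced left out | Safety population |
|---|---|---|
| 1 | 1/20 = 5.0% | 2/21 = 9.5% |
| 2 | 1/20 = 5.0% | 3/22 = 13.6% |
| 3 | 1/20 = 5.0% | 4/23 = 17.4% |
| 4 | 1/20 = 5.0% | 5/24 = 20.8% |

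The gap arises only if N=20 in 12.2 is taken as the safety denominator. Under 12.1, replacement by itself removes no event.

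**The case against.** The strongest reply is that the protocol already protects these children. Section 12.1 keeps every dosed child, replaced or not, in the primary safety analysis. Section 10.20 follows anyone who withdraws after an AE until it resolves or is stable, and 13.3 does the same for each AE. AEs are recorded from the first dose, and labs are due at Weeks +2 and +4. Footnote a does not forbid an earlier visit, so it can be read with 10.20 and 14.0 as mandatory after Week +8 and attempted before.

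Most of that stands. A reader might infer that the primary window loses the children most likely to have been harmed, so that AE incidence is biased downward. The documents do not support this: an event known to the site stays in the analysis, and an event would vanish only if it surfaced at a closing assessment that was never made and was also missed by the other follow-up. What the reply leaves open is narrower. Follow-up of a known AE does not call for labs that would reveal an unrecognised abnormality, and even the combined reading fixes no visit content before Week +8.

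On the count, it can be said that 13.0 concerns taking part in the study and 14.0 concerns taking the drug, and that families may decline to stay. Both are fair, and a count of zero needs every family to stay and a narrow reading of withdrawal. But the examples in objective 1 are reasons for stopping drug, so the two passages meet in exactly the children the measure is meant to capture.

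**Conclusion.** Two inconsistencies stand on the text. First, footnote a conflicts with 10.20 and 14.0 on early termination visits before Week +8, and footnote f depends on the visit; exit labs and a closing AE assessment are not assured in the primary safety window, with a last scheduled lab up to just under 4 weeks old. Second, the tolerability count in objective 1 depends on whether 13.0 or 14.0 is followed and can understate intolerance: 0% against 4.8% to 16.7% at the extremes, for an assumed 1 to 4 affected children.

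A loss of primary safety data or a downward bias in AE incidence is not demonstrated. The 5.0% against 9.5% to 20.8% comparison illustrates only a misuse of N=20, which 12.1 already rules out for the primary analysis. The point is worth correcting because visit triggers and withdrawal status are run by the site from this protocol.

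**What to change.** 1. In footnote a, delete only the lower limit ('after week +8 and'), and state that the visit applies to any dosed subject who leaves before Week +44, so that the same content, including safety labs, holds throughout. Refer to it from 10.20 and 14.0.
2. Reconcile 13.0 item 6 with 14.0 on follow-up and data collection for subjects who cannot tolerate treatment, and use one meaning of withdrawal throughout.
3. In 3.0, define the tolerability outcome as the number of dosed subjects who permanently stop drug or leave the study because of intolerability or AEs.
4. In 12.2, make clear that N=20 is the planned cohort and not the safety denominator, which under 12.1 includes dosed subjects who were replaced.

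The cost is a few wording changes and an occasional extra exit visit; its labs can use the home phlebotomy route already set up in 10.26.
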